### Intervention

The research group developed the PACT intervention, which consists of seven computerized and VR-based affective cognitive training tasks to provide an immersive and interactive experience. During each 1-h training session, participants engage in affective cognitive training tasks and reflect on how the practices and strategies learned during the training sessions can be effectively applied in their daily lives. The therapist will guide the participant in exploring various ways to integrate these techniques into their routine and adapt them to real-life situations.

In the first session, participants receive a detailed introduction to affective cognitive training, gaining an understanding of how and why affective cognitive processes are targeted. Participants' motivations and goals for the intervention are also discussed, and they receive a personal notebook to record their objectives. Throughout the following sessions, participants reflect on the practical application of each training task in their daily lives and document their experiences and progress in the notebook. The purpose of each computerized task is explained, its relevance to participants’ goals is discussed, and assistance is provided in translating the learned concepts to everyday life. In the final session, participants receive a leaflet containing information and exercises from the training sessions, discuss their benefits from the intervention, and are encouraged to continue practising what they have learned. The five training sessions are held over a period of approximately five weeks.

At the beginning of each session, participants select one of four different mindfulness VR scenarios lasting 5 to 10 min: a desert, a forest, the northern lights, or a beach by the sea. After the mindfulness exercise, participants complete an attentional bias modification (ABM) task and then proceed to the third task, which involves responding to infant videos with sensitive infant-directed facial expressions. The fourth task focuses on implicit emotion regulation training to enhance cognitive control abilities. Subsequently, participants engage in a cognitive bias modification (CBM) task that modifies negative cognitive biases in the perception of infants’ expressions. The sixth task involves explicit emotion regulation using mindfulness strategies and exposure to virtual reality scenarios, while the intervention concludes with a mindfulness-based visualization task.

The ABM, infant-directed facial expressions, and VR tasks utilize "biofeedback" technology, which employs real-time eye-tracking, facial expression analysis, and gaze analysis, respectively, to monitor participants’ responses to emotional infant signals. Continuous feedback is provided based on these responses for an effective and immersive training experience.

Attentional bias modification: In the ABM task, they watch infant videos on a laptop. Continuous information from real-time eye-tracking feeds back into the task and renders the video either blurred and red or clear depending on whether women look away or fixate on infant faces, respectively. This biofeedback directs participants’ attention toward infants’ faces. By repeatedly reinforcing attentional bias towards infant cues, this task aims to modify attentional biases away from intense infant emotion and promote more attentive responses to infant emotional stimuli.

Facial expression training: During the infant-directed facial expression task, women watch infant videos and are instructed to mirror infants’ emotional states with their facial expressions. An algorithm (Affectiva Affdex [53]) within the iMotions software continuously detects the participants’ facial expressions from facial action units (AUs), which are constantly estimated against predefined criteria for sensitive mirroring of specific infant emotions in real-life mother-infant interactions [54]. Participants receive feedback and modify facial expressions accordingly. This training enhances participants' reflection on the importance of facial expressions and communication with their infants, fostering a deeper understanding of the role facial expressions play in mother-infant interactions and promoting more effective non-verbal communication.

Cognitive and emotional control training: The cognitive control training task is a verbal letter-variant* N*-back task, with distracting infant cry sounds coming and going. Participants are instructed to indicate when a letter presented on the screen matches the one displayed *N* steps back by pressing a key. Participants are instructed to focus on the task even when infant cry sounds appear. By training participants to sustain attention and inhibit distractions, this task strengthens their cognitive control abilities, which are crucial for effective emotion regulation.

Cognitive bias modification: In the CBM task, women watch infant emotional face images each presented for 2 s. and are asked to evaluate, as fast as possible, whether the infant is happy or distressed after which they receive feedback corresponding to the emotion displayed. For 10 ambiguous infant faces, participants are continuously told that the infant is happy, which lowers the threshold for perceiving infant happiness.

Virtual reality-based emotion regulation training: Virtual reality-based emotion regulation training incorporates exposure to being with an infant, allowing participants to gradually acclimate to the presence of infants in a controlled environment. The VR scenario presents a playroom-like environment with various toys. In the VR scenario, participants are immersed in situations where infants are crying, laughing, or relaxing, with one infant present at a time. At the beginning of each VR scenario, participants are instructed by a voice-over and provided with a specific emotion-regulation strategy that focuses on their attention and focus. They are instructed to maintain visual contact with the infants’ faces while applying this strategy. To reinforce attention towards the infant, a “circle” within the VR scenario guides participants' attention back to the infant if they gaze away. By practising this task, participants improve their emotion regulation skills by learning methods to remain calm, direct their attention towards the infants rather than their own emotions, and consider the needs of the infants. This immersive virtual reality experience provides a safe and controlled environment for participants to develop and enhance their ability to regulate their emotions effectively in real-life interactions with infants.

Visualization of the baby: The visualization task involves a short meditation, where participants are instructed to breathe, close their eyes, visualize themselves with their baby, and send loving, kind, and warm thoughts and feelings toward the baby in their tummy. Through engaging in the visualization exercise, participants can cultivate a positive emotional connection with their unborn child, fostering feelings of care and bonding, and ultimately reducing depression by providing a sense of emotional well-being during pregnancy.

Care as usual: Participants receiving CAU will receive the standard care provided to pregnant women without any additional experimental interventions. It typically involves routine prenatal care, which may include regular check-ups, medical assessments, and general support from healthcare professionals. In some cases, high-risk pregnant women with a history of severe mental illness may receive additional specialized care, such as more consultations with midwives or the consideration of psychotropic medication, to address their specific needs and ensure their well-being throughout pregnancy.

### Materials

Computerized testing and training are run on a Lenovo IdeaPad Gaming 3 15.6" laptop using E-prime version 2.0 and iMotions Software version 9.0 and integrated biosensor hardware (iMotions A/S, Copenhagen, Denmark) including eye-tracking (Smart Eye AI-X) [55–57], galvanic skin responses (GSR) and facial expression analyses [53]. Training and testing VR scenarios are created in collaboration with the VR company Khora. Specifically, eight 4–9-month-old infants were video filmed with an Insta Titan camera, recordings were edited in Premiere Pro and VR scenarios programmed in Unity software and were run on an HTC Vive 2 Eye VR headset for baseline tests and a PICO VR headset for training sessions. The interpersonal synchrony of brain activity between mother and child is measured using fNIRS with the Artinis system, which includes BabyBrite, PortaSync hardware, and OxySoft software.

#### Clinical assessments, interviews, and questionnaires

At baseline T0, participants fill out questionnaires regarding their stress levels, sleep, relation to own parents, unborn child and partner, and depressive symptoms with the State and Trait anxiety questionnaire (STAI-S and T) [58], Pittsburgh Sleep Quality Index [59], Perceived stress [60], Parental Bonding Inventory [61], Maternal Antenatal Attachment Scale [62], Experiences in Close Relationships, Cognitive Emotion Regulation Questionnaire [63] and Edinburgh Postnatal Depression Scale (EPDS) [73, 74]. The EPDS is the internationally most widely used screening tool for PPD and in the Danish population, a cut-off of 11 or higher is the most indicative when screening for PPD [64]. They also rate their experience in VR with the Multimodal Presence Scale [65]. As mentioned previously, participants also fill out the ANRQ [66], which is used to determine their risk status for PPD.

At baseline, participants are interviewed with the HDRS-6 [51, 67], the Standardized Assessment of Personality – Abbreviated Scale (SAPAS) [68] and assessed with the Screen for Cognitive Impairment in Psychiatry (SCIP) [69].

Six months postpartum, mothers undergo an interview utilizing the Present State Examination (PSE), a component of the Schedules for Clinical Assessment in Neuropsychiatry (SCAN) [70], to assess the presence of depressive episodes since childbirth. The clinicians conducting the diagnostic interviews have received specific training and ongoing supervision from the project leader to ensure valid and reliable assessments.

Further, mothers rate their emotions when their child cries with the My Emotions Questionnaire [68]; they fill out the Postpartum Bonding Questionnaire [69] and Parental Stress Scale [70] and evaluate their child’s development with Ages-and Stages Questionnaire: Socio-Emotional (ASQ:SE) [71]; and their reflective functioning is assessed with Parental Reflective Functioning Questionnaire (PRFQ-1) [72].

Mother-infant interaction videos from 8 to 13 months after birth follow-up will be coded with the manual-based tool Coding Interactive Behaviour (CIB) [71] and infant development will be assessed with the Bayley Scales of Infant and Toddler Development 4th edition [72, 73]. Both assessments are conducted by trained researchers blind to group status.

#### Data entry, coding, security, and storage

All data entry for this trial will be conducted directly into REDCap, a secure web application designed for research data capture. REDCap ensures high data quality through several mechanisms: field validation, e.g. ensures that dates are correctly formatted and within specified ranges, and that numerical values fall within predetermined limits. Essential fields are marked as required to prevent missing data, for example when participants fill out questionnaires. REDCap is hosted on a secure server. Access to the system is restricted to authorized personnel through unique user credentials, ensuring data confidentiality and integrity. All data will be collected electronically via REDCap by trained research staff, ensuring consistency and accuracy, and eliminating the need for paper-based Case Report Forms (CRFs).

The study is conducted in compliance with existing laws on data protection. Any changes to the protocol will be submitted for approval to the Ethics Committee. Deviations from the protocol will be documented, and the protocol will be updated in the clinical trial registry as necessary. To ensure confidentiality, all data collected during the course of the research will be kept strictly confidential, pseudonymized and accessed only by members of the trial team. Participants will be allocated a pseudonymous ID number to protect their identities. Data from interviews, ratings, questionnaires, and cognitive tests are in REDCap, a secure web application for research data capture. Computerized test data are also stored securely on a server within the Mental Health Services, Capital Region of Denmark. In the current trial, we are collecting hair samples from participants for hair cortisol analyses. These samples will be analysed in one batch after all data collection is completed. The hair samples are kept in envelopes labelled with the participant's ID number and the date of collection. The envelopes are stored securely in a locked cabinet within a locked office. The hair samples will not be kept for future ancillary studies. The de-identified data will be securely stored for ten years after data collection has ended and will then be deleted.

### Outcome measures

The *primary outcome* is the difference between mothers receiving PACT versus CAU in (i) the incidence of PPD during the first six months after birth, assessed with the Present State Examination (PSE), which is a part of Schedules for Clinical Assessment in Neuropsychiatry (SCAN) [70].

The *three secondary outcomes* are differences between participants receiving PACT and CAU in (i) severity of depressive symptoms during the first six weeks after birth, (ii) the reduction in negatively biased cognitive processing of infant stimuli from baseline to follow-up during pregnancy (T1), and (iii) the self-rated parental stress six months after birth.

*Tertiary outcomes* involve assessing differences in infant development, mother-infant interaction measures (e.g. sensitivity, intrusiveness, dyadic reciprocity), and changes in facial expressions and visual attention towards infant stimuli (during pregnancy) between the PACT and CAU groups.

### Statistical analyses

Group differences in the prevalence of PPD will be analysed with generalized mixed model and linear mixed models, respectively. Group differences in affective cognitive changes from baseline to follow-up (in pregnancy) will be analysed with linear mixed models. We will apply appropriate imputation methods before fitting the model to address missing data concerns. With mediation analyses, we will investigate if depressive symptoms and the prevalence of PPD after birth are mediated by changes in affective cognition. Associations between affective cognitive performance on training tasks and changes in affective cognitive outcomes and PPD prevalence will be explored with regression analyses. All analyses will involve adjustment for variables on which participants may differ at baseline, including socio-demographic factors, attachment feelings to the unborn child, child gender, clinical history, and depressive symptoms during pregnancy. We will use the SPIRIT reporting guidelines [74].

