## Background and aim

Postpartum depression (PPD) is a severe mental illness with a prevalence of around 8% for women with no history of depression [1, 2] and 30–50% for women with a history of previous depression or bipolar disorder (mania and depression) [3–7]. Multiple factors are associated with risk of PPD, including a history of depression, unwanted pregnancy, low emotional support, low socio-economic status [8] pregnancy complications [4, 9–11], weak attachment feelings to the unborn child [12, 13], and emotion regulation difficulties [14]. Emerging evidence indicates that negative cognitive bias in the perception of infant cues and reactivity to infant distress plays a key role for the risk of PPD. For example, we showed that more negative ratings of infant crying during pregnancy were associated with a substantially increased risk of PPD with an odds ratio of 3.75 [15]. This finding is in line with evidence that negative cognitive bias is a risk and maintaining factor for depressive episodes [16, 17]. Pregnant women at known risk of PPD are commonly offered prophylactic *pharmacologic* interventions, most commonly with selective serotonin reuptake inhibitors (SSRIs) [18]. However, many pregnant women are reluctant to accept pharmacological interventions due to their potentially harmful effects on the foetus [19–21]. Psychological interventions, including talk therapy, psychoeducation, and midwife consultations, have been found to reduce PPD symptoms [22–26]. However, these interventions generally focus on *detecting and treating* rather than *preventing* PPD [27]. *Psychological preventive* strategies in pregnant women *before* PPD onset are thus urgently needed.

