### Aims and hypotheses

The aim of this randomized controlled trial (RCT) is to investigate the potential prophylactic effects of a short-term (5 weeks) prenatal affective cognitive training (PACT) intervention that combines computer and virtual reality-assisted techniques compared with care as usual (CAU) for pregnant women at heightened risk of postpartum depression (PPD). Furthermore, pregnant women who do not meet the inclusion criteria for the high-risk group, are included in the study and assessed at baseline during pregnancy and follow-up after birth. This allows us to explore the risk factors that predict PPD among all pregnant women. We hypothesize that (i) PACT reduces the incidence of PPD during the first 6 months postpartum, and the severity of depressive symptoms during the first 6 weeks postpartum and (ii) the effect of PACT on PPD onset and depressive symptoms after birth is mediated by change in affective cognitive responses to infant stimuli.

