### Statistical power calculation

In a previous study from our group on affective cognition in high-risk pregnant women, 50% went on to develop PPD [15]. On average, these women rated infant cries 0.47 standard deviations *more negatively* than high-risk women who remained healthy. Hence, 83% of high-risk women who went on to develop PPD, exhibited a negative bias in their responses to infant cries during pregnancy compared with 48% high-risk women who remained healthy. Therefore, targeting negative affective cognitive response to infant emotion may reduce the risk of PPD. Based on this PPD incidence of 50% [15], we aim to demonstrate a clinically significant reduction of the incidence of PPD from 50 to 25% (i.e. reducing the risk to half). To reach a statistical power of ≥ 80% for detecting this effect at a two-sided 0.05 alpha level, we need a sample of *n* = 58 pregnant high-risk women with complete data per intervention arm (https://clincalc.com/stats/samplesize.com). To accommodate for an expected dropout rate of up to 20% (as in our pilot study), we aim to include *n* = 73 women per treatment arm, i.e. *N* = 146 trial participants in total.

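### The mediator is the change in affective cognition, and its baseline value is not a named covariate; if the baseline value is left out, the mediator–outcome path can be attenuated

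*Protocol article*

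**What the plan says.** Hypothesis (ii), under Aims and hypotheses, is that the effect of PACT on PPD onset and depressive symptoms "is mediated by change in affective cognitive responses to infant stimuli". The Statistical analyses section repeats this choice of mediator: "we will investigate if depressive symptoms and the prevalence of PPD after birth are mediated by changes in affective cognition". No mediation equations are given.

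The same section has one adjustment rule: "All analyses will involve adjustment for variables on which participants may differ at baseline, including socio-demographic factors", and the list continues with "attachment feelings to the unborn child, child gender, clinical history, and depressive symptoms during pregnancy". The T0 value of affective cognition is not named. The list is introduced by the word *including*, so it is not closed.

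Two other sections connect the level of bias, as distinct from its change, to later PPD. Background and aim reports that more negative ratings of infant crying in pregnancy went with a "substantially increased risk of PPD with an odds ratio of 3.75". The Statistical power calculation says of the women who developed PPD that, on average, "these women rated infant cries 0.47 standard deviations" more negatively than high-risk women who stayed well. It adds that 83% against 48% showed a negative bias.

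**The concern.** Randomisation balances T0 bias between arms, but within each arm T0 bias still varies and is part of the change score. A woman with a high T0 score tends to show a larger fall by T1 through regression to the mean. On the article's own evidence, she also tends to have a higher PPD risk. If T0 is not in the outcome model, this pulls against the expected relation between improvement and lower risk.

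The stated criterion, variables on which participants may differ at baseline, does not reliably bring T0 in. Read as imbalance between arms, it gives no reason to add T0 bias when the arms are balanced, yet the problem remains.

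What is at stake is the answer to hypothesis (ii), which Dissemination of results assigns to the second planned article. The trial could report no mediation when the proposed mechanism is real.

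**Working it through.** **Inputs from the article.** The mediator is T1 − T0 change. Both scores are collected in all high-risk women (Procedure). The complete-case target is 58 per arm, or 116 in total (Statistical power calculation).

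**Not given, so assumed.** The T0/T1 SD ratio k is 0.5 to 1.5, the T0–T1 correlation r is 0.3 to 0.7, and b1 = 0.5 with b0 from −b1 to b1.

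**1. The plan's own figure.** The only sample size is for the primary outcome. For 50% against 25%, two-sided 0.05, 80% power, pooled and without continuity correction:

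n = [1.960·√(2 × 0.375 × 0.625) + 0.842·√(0.25 + 0.1875)]² / 0.25² = 57.7, so 58 per arm. Then 58/0.8 = 72.5, so 73.

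Both stated figures reproduce. There is no stated figure for mediation.

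**2. Path without T0.** Within an arm let Y = b1·T1 + b0·T0 + e, with SDs s1 and s0, and D = T1 − T0. The coefficient of Y on D is

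[b1(s1² − r·s0·s1) + b0(r·s0·s1 − s0²)] / (s0² + s1² − 2r·s0·s1).

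With s0 = s1 the numerator is s²(1 − r)(b1 − b0) and the denominator is 2s²(1 − r). The path is therefore (b1 − b0)/2 for any r: one half of b1 if b0 = 0, one quarter if b0 = b1/2, and zero if b0 = b1.

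**3. Unequal SDs.** Share of b1 retained, for r from 0.3 to 0.7:

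| k = s0/s1 | b0 = 0 | b0 = b1/2 | b0 = b1 |
|---|---|---|---|
| 0.5 | 0.89 to 1.18 | 0.84 to 1.27 | 0.79 to 1.36 |
| 0.7 | 0.74 to 1.00 | 0.61 to 1.00 | 0.48 to 1.00 |
| 1.0 | 0.50 | 0.25 | 0.00 |
| 1.3 | 0.32 to 0.10 | −0.02 to −0.34 | −0.36 to −0.79 |
| 1.5 | 0.23 to −0.04 | −0.15 to −0.57 | −0.53 to −1.09 |

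For b0 = 0 the share is (1 − rk)/(1 + k² − 2rk). At k = 0.7, r = 0.3 this is 0.79/1.07 = 0.74. At k = 1.3, r = 0.7 it is 0.09/0.87 = 0.10. If b0 = −b1, so that the outcome follows change itself, the share is 1.00 throughout.

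**4. Path with T0.** Since b1·T1 + b0·T0 = b1·D + (b1 + b0)·T0, the coefficient on D is b1 once T0 is in the model. T1 and change then give the same path.

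**5. What the article implies about b0.** With equal SDs, cov(T0, Y) = s²(r·b1 + b0). A positive link between T0 bias and PPD needs b0 > −r·b1, so the share retained is below (1 + r)/2: below 65%, 75% and 85% at r = 0.3, 0.5 and 0.7. The fully unbiased case, b0 = −b1, gives cov(T0, Y) = −b1(1 − r)s², so higher baseline bias would go with lower risk. The article reports the opposite direction.

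**6. Simulation.** Assumptions: standard normal scores with equal SDs, a 0.5 SD arm effect on T1, no direct arm effect, and b1 = 0.5 (per SD, or log odds per SD for PPD). With n = 200,000, the path without T0 was about 0.25, 0.12 and 0.00 (linear) and 0.24, 0.11 and 0.00 (logistic) for b0 = 0, 0.25 and 0.50. With T0 it was 0.49 to 0.51. Power for the mediator–outcome path at n = 116 (600 trials), without vs with T0:

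| b0 | r | Continuous symptoms | Binary PPD |
|---|---|---|---|
| 0 | 0.5 | 69% vs 99% | 22% vs 62% |
| 0 | 0.7 | 42% vs 97% | 14% vs 43% |
| 0.25 | 0.5 | 20% vs 99% | 9% vs 56% |
| 0.25 | 0.7 | 12% vs 96% | 6% vs 42% |
| 0.50 | 0.5 | 5% vs 99% | 6% vs 55% |
| 0.50 | 0.7 | 7% vs 95% | 6% vs 39% |
| −0.50 | 0.5 | 100% vs 99% | 75% vs 64% |
| −0.50 | 0.7 | 97% vs 96% | 53% vs 46% |

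These figures rest on the assumed values and leave out the other listed covariates, some of which may carry part of the T0 information.

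**The case against.** The strongest objection is that the defect depends on T0 being left out, and the article never says that it is. The covariate list is open, T0 affective cognition is measured, and an article may leave the mediation equations to a fuller document. This stands in part: a reader might infer that the plan excludes baseline bias, and the text does not support that. But the article does fix a change-score mediator and a criterion for adjustment, and an analyst could follow both faithfully and omit T0.

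A second objection is that the size is indeterminate. This stands. A reader might infer that the path is certain to be halved or lost. Halving needs equal SDs and b0 = 0, and complete loss at equal SDs needs b0 = b1; the article gives none of these. Entry on a score of 96 or more out of 100 could narrow the T0 SD and weaken the attenuation, although women can also enter through the ANRQ alone. The odds ratio of 3.75 is compatible with b0 = 0 and does not show an effect of T0 bias beyond T1 bias.

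Third, the pilot found that treatment-related reduction in bias correlated with fewer symptoms at six months. That supports a link with change, but it comes from a non-randomised study in which 12 of 16 women completed all assessments, and an attenuated path can still be positive.

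Finally, mediation is not among the listed primary, secondary or tertiary outcomes. That limits the weight of the point, but mediation remains one of two stated hypotheses.

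**Conclusion.** The point holds in conditional form. The article sets change as the mediator, does not name the T0 value as a covariate, and itself supplies evidence that the level of bias matters for PPD. If T0 is omitted, the mediator–outcome path and the indirect effect can be attenuated. With equal SDs the path is half the true one when only T1 bias acts, and zero when T0 and T1 bias act equally. With b0 = 0 the retained share runs from 74–100% at an SD ratio of 0.7 to 10–32% at 1.3, and at more extreme ratios it can exceed 100% or turn slightly negative.

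The SDs, correlation and slopes behind these figures are assumptions, so no single percentage or power figure should be quoted as the trial's loss. The primary analysis and the randomised arm-to-mediator path are untouched. This should be corrected because it bears on the conclusion for hypothesis (ii), but it does not threaten the main result.

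**What to change.** Add one sentence to Statistical analyses: the T0 score of the same affective-cognition measure enters both the mediator model and the outcome model, with the T1 score (or equivalently the change) as mediator. The wording of hypothesis (ii) can then stand. Depressive symptoms during pregnancy are already listed as a covariate and need no addition. If power for mediation is reported, give it as a range over stated assumptions, separately for continuous symptoms and binary PPD.

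The cost is one covariate per model and no new data, since T0 and T1 are already collected. The sentence should be in place before the outcome data are analysed; at the June 2024 revision, final follow-up was expected to end in July 2025.
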